### **11.8.2 Clinical Laboratory**

No clinical laboratory data are being recorded.

### **11.8.3 Physical Examination and Other Safety Measures**

No safety assessments are being performed

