**Safety**

Common Terminology Criteria for Adverse Events (CTCAE) 5.0 grading for acute and late effects, relevant to treatment:

- Radiation dermatitis
- Skin ulceration
- Alopecia
- Skin induration
- Hypo/hyperpigmentation

- Telangiectasia

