### **5.5 Safety Endpoint**

- Safety: Adverse events (AEs) by severity and by relationship to Rhenium-SCT, including radiation dermatitis, skin ulceration, alopecia, skin induration, hypo/hyperpigmentation, and telangiectasia.

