| Photos via App*                                                |                     |                                     |                                       |                                        | X                                                                        |                                        |                            |                            |                                                       |                        |
| Photography at site follow up visits (site camera)             |                     | X                                   |                                       | X                                      |                                                                          |                                        | X                          | X                          | X                                                     | X                      |
| CTCAE grading/wound assessment                                 |                     |                                     |                                       | X                                      |                                                                          |                                        | X                          | X                          | X                                                     | X                      |
| QoL questionnaire* via App                                     |                     | X                                   |                                       |                                        |                                                                          |                                        |                            | X                          | X                                                     |                        |
| Comfort of treatment* via App                                  |                     |                                     |                                       | X                                      |                                                                          |                                        |                            |                            |                                                       |                        |

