| Histology if lesion visible/suspected/or per clinical practice |                     |                                     |                                       |                                        |                                                                          |                                        |                            |                            | X                                                     | X                      |

|                                                            |  |  |  |  |  |  |  |  |  |   |
|------------------------------------------------------------|--|--|--|--|--|--|--|--|--|---|
| Review for wound complications or radiation changes |  |  |  |  |  |  |  |  |  | X |
|------------------------------------------------------------|--|--|--|--|--|--|--|--|--|---|

\*QoL, subject rated cosmetic outcome, monthly photos obtained through subject trial App; \*\* baseline visual RECIST is to measure lesions only; \*\*\* AE's to be recorded for the first 30 days post treatment. After this only treatment related AEs are to be recorded: \*\*\*\* Histology must be confirmed to meet the inclusion criteria before any baseline assessments are conducted

AE: Adverse events; QoL: Quality of life; RECIST: Response evaluation criteria in solid tumours

NOTE: In case of early termination: In case of premature termination during the follow-up period, the investigator shall endeavour to arrange a premature end of study visit and perform examinations according to end of treatment visit. If the subject does not enter the follow-up period, this is the study termination (end of study) visit.

NOTE: Radiation changes at months 24 are to be recorded as the CTCAE grading in protocol appendix 1, excluding Radiation dermatitis.

NOTE: Subjects who do not have a smart phone will complete QoL questionnaire, Comfort of treatment questionnaire and Cosmetic outcome on paper questionnaires at the follow up visits. Monthly photos are not taken for subjects without a smart phone, instead photos are taken at the site, at follow-up visits only.

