#### **3 month follow up visit:**

- Concomitant medications
- Photography of treated lesions (medical photographer or site digital camera)
- CTCAE grading (see protocol appendix 1)
- AEs

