**24 month follow up visit:**

- Photography of treated lesions (medical photographer or site digital camera)
  - CTCAE grading. Grading can be found in protocol appendix 1
  - Cosmetic outcome; subject rated. To be completed on Trial app (or directly into the eCRF if subject does not have a smart phone). VAS image found in the protocol appendix 3
  - Cosmetic outcome: Clinician rated. To be completed into the eCRF using VAS in the protocol appendix 3
  - Modified Visual RECIST assessment. Guide to assessment is found in protocol appendix 5
- 
- Histology to be performed if lesion is visible, suspected or is the site's regular clinical practice
  - General review for wound complications and radiation changes. Radiation changes at months 24 are to be recorded as the CTCAE grading in protocol appendix 1, **excluding** Radiation dermatitis.

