## **11.8 Safety Analyses**

### **11.8.1.1 Adverse Events**

Adverse events will be coded using MedDRA and comprehensively summarised by System Organ Class (SOC) and Preferred Term (PT) overall, by severity and by relationship to Rhenium-SCT.

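### Section 11.8.3 denies that safety assessments are performed, although skin toxicity is graded at five visits, and nothing secures late grades a place in the one planned safety summary

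*Protocol*

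**What the plan says.** Section 11.8.3, the part of the analysis section reserved for physical examination and other safety measures, consists of one statement: "No safety assessments are being performed".

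Elsewhere the protocol schedules such assessments:

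- Table 2 has a row for "CTCAE grading/wound assessment", marked at the 14-day visit and at months 3, 6, 12 and 24, and a row for "Review for wound complications or radiation changes", marked at month 24.
- The visit lists in section 9.1.3 repeat the grading. The 3-month list has "CTCAE grading (see protocol appendix 1"), and the 24-month list adds "General review for wound complications and radiation changes".
- The synopsis gives as its safety criterion "Common Terminology Criteria for Adverse Events (CTCAE) 5.0 grading for acute and late effects, relevant to treatment".

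The safety endpoint in section 5.5 is "Adverse events (AEs) by severity and by relationship to Rhenium-SCT, including radiation dermatitis, skin ulceration, alopecia, skin induration" and the remaining skin effects. The matching analysis in section 11.8.1.1 reads "Adverse events will be coded using MedDRA and comprehensively summarised by System Organ Class (SOC) and Preferred Term (PT) overall, by severity", and also by relationship to treatment.

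**The concern.** The statement in section 11.8.3 is not an omission that a later analysis plan would simply fill. It says that the data do not exist. An analysis plan that follows it would plan no summary of the visit grades, and one that plans such a summary would contradict the protocol. Section 9.4 (Safety Assessments) does not correct the error, because it does not mention the CTCAE grading.

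What is at stake is the late-effects profile. The synopsis asks for late as well as acute effects, and the fixed-visit gradings are the trial's systematic record of them. If these reach the report only when a site also enters them as AEs, the late profile depends on a recording step that the protocol does not describe and, after Day 30, on a relatedness judgement made in an open-label study.

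**Working it through.** The protocol gives no figure to reproduce. The check compares the schedule with the AE collection rules and then counts the gradings exposed.

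**Step 1. Where grading and AE recording are listed (Table 2 and sections 9.1.2 to 9.1.3).**

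| Visit | Grading, Table 2 | Grading, visit text | AEs, Table 2 | AEs, visit text |
|---|---|---|---|---|
| Day 0 | no | no | yes | yes |
| Day 14 | yes | no | yes | no |
| Day 30 call | no | no | yes | yes |
| Month 3 | yes | yes | no | yes |
| Month 6 | yes | yes | no | yes |
| Month 12 | yes | yes | no | no |
| Month 24 | yes | yes | no | no |

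Grading is scheduled at five visits. At months 3 and 6 the visit lists show grading and AEs as separate items. At months 12 and 24 they show grading and no AE item.

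**Step 2. What reaches the AE pages after Day 30.** The Table 2 footnote and sections 10.1 and 10.5 keep only AEs judged treatment related. Section 10.4 allows the investigator to exclude association for events later than 30 days, and such events are then not recorded. Section 10.6 asks for all serious events to 90 days, which widens the net for serious events only. No section says that a grade recorded at a visit must be entered as an AE.

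**Step 3. Number of gradings exposed.** Appendix 1 has 7 terms: radiation dermatitis, skin ulceration, alopecia, skin induration, hypopigmentation, hyperpigmentation and telangiectasia. Radiation dermatitis is excluded at month 24.

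- Months 3 and 6: 7 × 2 = 14
- Month 12: 7
- Month 24: 7 − 1 = 6
- Total after Day 30: 14 + 7 + 6 = 27
- Of these, at visits with no AE item in either place: 7 + 6 = 13

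The Day 14 visit adds 7 gradings (27 + 7 = 34 in all), but AEs are collected to Day 30 whatever their relationship, so the relatedness rule does not touch those 7.

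**Step 4. What the AE table can show.** A summary by system organ class and preferred term counts reported events. It does not show how many subjects were graded at month 12 or 24. Subjects leave the study on progression or further treatment (section 9.1.4), so that number will be smaller than the number treated. Grade prevalence or persistence at a visit cannot be read from such a table.

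**The case against.** The strongest reply is that these toxicities do have an analysis. Section 5.5 names them as AEs by severity and relationship, section 10.5.2 grades AE severity by CTCAE version 5.0, and section 11.8.1.1 tabulates AEs by severity. This stands. A reader might infer from section 11.8.3 that the late-toxicity data have no analysis at all. The documents do not support that, because any graded finding entered as a related AE would be tabulated.

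Four further points:

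- In-field skin changes are likely to be called related, and section 10.5.4 puts weak or unassessable relationships under possible rather than not related. This lowers the likely loss. It does not remove it, since the protocol does not say whether a possible relationship counts as related for collection after Day 30.
- The 24-month review is largely not a separate dataset. Radiation changes at that visit are to be recorded as CTCAE grades, so only wound complications lack a stated format. This stands.
- By-visit tables are commonly left to the analysis plan, and section 11.2 says one will be written. This stands for table layout. It does not excuse a protocol statement that the assessments are not performed.
- The sentence may be a loose way of saying that nothing beyond AEs is measured. Even so, it is untrue: a scheduled grading is a measure beyond AEs.

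**Conclusion.** The point holds in a limited form. Section 11.8.3 is a false statement in the analysis section, contradicted by Table 2, the visit lists and the synopsis. Separately, the protocol does not link visit grades to AE records, and the link is weakest at months 12 and 24. Up to 27 scheduled term-by-visit gradings can fall outside the only planned safety summary, 13 of them at visits with no AE item.

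The 27 is an upper bound on schedule cells, not an estimate of lost data. It assumes that no grade after Day 30 is entered as a related AE, and the documents give no basis for saying how many would be. A reader might also count all 34 gradings as exposed. The 7 at Day 14 should not be counted, because all AEs are collected then. The primary efficacy analysis is not affected.

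**What to change.** Replace the text of section 11.8.3 with wording to this effect:

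> CTCAE grading and wound assessment are performed at 14 days and at 3, 6, 12 and 24 months. For each Appendix 1 term, the number and percentage of subjects at each grade (worst across their treated target lesions), among those graded, will be tabulated by visit and as worst post-treatment grade, whether or not the finding was entered as an adverse event. Wound complications found at the 24-month review will be summarised. Radiation changes at that visit are covered by the CTCAE table.

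This settles the unit (subject, although up to three target lesions may be treated) and the denominator, and it frees the summary from the Day 30 relatedness rule. Month 24 has no radiation dermatitis row, as the protocol already specifies.

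The cost is a few extra tables. No visit, assessment or clinical rule changes, and the data are already being collected.

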## **11.9 Subgroup Analyses**

All analysis models will include tumour type (BCC/SCC) as a factor. As described above, for all analyses, the results will be presented overall and by tumour type

## **11.10 Interim Analyses**

An interim analysis is planned once 50% of subjects have completed 6 month follow up visit.

The purpose of the interim analysis is to provide an early indication of the effects of treatment on patient reported outcomes (namely QOL and subject report comfort of treatment). No amendments to the study are planned on the basis of the interim analysis results. The results may be published or presented at a conference.

Subject recruitment will not be paused for the interim analysis.

## **11.11 Handling of Dropouts and Missing Data**

The reason for withdrawal will be summarised. For all efficacy assessments, all available data will be used. No imputation for missing data will be implemented.

Modified Visual RECIST assessment

- Histology to be performed if lesion is visible, suspected or is site clinical practice

## **12. DATA COLLECTION, HANDLING, AND RECORD KEEPING**

### **12.1 Generation of Data Base**

The eCRF will be supplied by the CRO and should be handled in accordance with the instructions provided. eCRFs will be provided as regulatory compliant, electronically secure and protected, web-based database. An audit trail will record all entries and corresponding changes.

All eCRFs should be filled out completely by qualified personnel or authorized study staff. Only authorized persons will be granted access. After the last query for a subject is closed, the eCRF is reviewed by the investigator and signed electronically.

### **12.2 Data Collection**

All study data are to be recorded in the eCRF.

All the subject's data have to be reported on the eCRF in a pseudonymized fashion, the subject only being identified by the subject number.

The investigator will be responsible for the completeness, accuracy and legibility of the information in the eCRF and other study documents. Data derived from source documents are to be consistent with these source documents.

The study monitors check the eCRF against the source documents for accuracy and validity according to the monitoring schedule, as applicable.

Upon completion of the examination, eCRF completion is expected at each site within 5 days of the subject visit, to ensure quality of data and subject safety. Once eCRF are completed, they will be available for review by the monitor and the clinical data management. Completed eCRF will be reviewed remotely for logical discrepancies. The monitor will ensure that all data queries and subsequent amendments in the eCRF documentation are made according to GCP guidelines.

The trial will have an associated App, available for Apple and Android smart phones, through which the following data will be collected (and will be directly populated into the eCRF):

- QOL questionnaire prior to treatment, anytime during the screening period, after consent has been given, and the subject has been enrolled into the study
- Comfort of treatment, recorded within 14 days post-treatment with Rhenium-SCT
- Subject rated Cosmetic Outcome recorded at 12 months and 24 months post-treatment
- Monthly photos for general visual assessment

If the subject does not have a smart phone, then monthly photos are not taken and all other PROM data is collected at follow visits and then entered into the eCRF. Questionnaires and VAS can be found in the protocol appendix 3.

Upon enrolment into the study, and once the subject's informed consent has been obtained, the eCRF will generate a unique App code for the subject.

The subject will download the trial App from the Apple Store or Google Play and enter this unique code in order to access the App and its functionality.

No data recorded via the App is stored on the phone for privacy compliance. All data is immediately transferred from the App to the eCRF or a secure server.

Photos taken by the subject via the Trial App should be:

- Taken with a ruler next to each lesion. The ruler will be supplied by the site. The subject may need the assistance of a family member or friend to take the photos if the target lesion is difficult to reach.
- Two separate photos of each target lesion are to be taken: one in indoor light, and one in natural light. The App will prompt the subject accordingly.

The app will pop up notifications at timepoints at which subject reporting is required.

### **12.2.1 Source Data**

Source data is all information, original records of clinical findings, observations, or other activities in a clinical study necessary for the reconstruction and evaluation of the study. Source data are contained in source documents. Examples of these original documents and data records include hospital records, physician's and nurse's/technician's notes, clinical and office charts, laboratory notes, pharmacy dispensing records, recorded data from automated instruments, consultant letters, screening and enrolment log, etc.

The investigator is responsible to keep all study-related source data enabling the sponsor to reconstruct the complete course of the clinical study. Source data will be transcribed to and reported through the eCRF accordingly.

## **12.3 Data Management**

All data management activities will be done according to FDA CFR-part 11 as required by regulatory agencies. Responsibility for data management lies with the designated CRO following their internal standard operating procedures (SOPs).

The designated CRO will be responsible for the activities associated with the data management of this study, including the production of an eCRF, setting up a relevant database, along with appropriate validation of data and resolution of queries. All data will be entered into the eCRF. Automated and manual checks will be made against the data to ensure completeness and consistency.

Clean data sets will be provided for statistical analysis and reporting.

## **12.4 Data Protection**

The data obtained during the study will be treated pursuant to the EU General Data Protection Regulation (GDPR) and national laws on data protection.

Generally, all subject related data is recorded in a pseudonymized manner to effectively mitigate the possibility to attribute clinical data to a person in accordance with data protection regulations.

During the clinical study, subjects will be identified solely by means of their individual identification code (Subject ID). Study data stored on a computer will be stored in accordance with local data protection law and will be handled in strictest confidence (e.g., preventing

unauthorised use of the system by password-protection, limited-rights management of authorized personnel, security screening of access to data, access monitoring and an access log of subject data). Distribution of these data to unauthorized persons must be strictly prevented. Data from subjects including imaging analyses, central lab measurements and their results is therefore only accessible to designated personnel on the study and is password-protected. The appropriate regulations of local data legislation will be fulfilled in its entirety.

The subject consents in writing to release the investigator from his/her professional discretion in so far as to allow inspection of original data for monitoring purposes by health authorities and authorized persons (inspectors, clinical monitors, auditors). Authorised persons (inspectors, clinical monitors, auditors) may inspect the subject-related data collected during the study in accordance with the data protection law.

The investigator will maintain a subject identification list (Subject IDs with the corresponding subject names) to enable records to be identified. This list will be stored in the clinical data repository, which is an access-restricted room. Subjects who do not consent to circulate their pseudonymised data will not be included into the study.

This protocol, the CRFs and other study-related documents and material must be handled with strict confidentiality and must not be disclosed to third parties except with the express prior consent of Sponsor. In particular, it must be ensured that the study medication is kept out of reach of third parties. Staffs of the investigators involved in this study are also bound by this agreement.

Electronic data will be handled according to best business practices including, but not limited to, use of appropriate system login details (e.g., for data capturing and management systems), systemic up-to-date virus/malware detection, firewalls, and back-up and restore processes.

In accordance with Oncobeta Therapeutics Australia's SOPs, providers' processes and systems are regularly audited to check their compliance with clinical study related guidelines and regulations and data protection regulations. Reporting procedures include the reporting of breaches as well, enabling Oncobeta Therapeutics Australia to meet such regulatory expectations.

In the unlikely event that un-pseudonymised personal subject data would be received by the sponsor, those would be immediately destroyed by the recipient according to the sponsor's policy.

If the study personnel at the clinical study site becomes aware that a personal data breach has occurred the competent supervisory authority (University Hospital Administration, legal department and law-enforcement institutions) should be notified immediately, i.e., no later than 72 hours after having become aware of it. In the case of the breach is unlikely to result in a risk for the health, rights and freedoms of individuals, the next steps can be discussed and actions to prevent further breaches are installed. The notification of a breach should contain the following key components:

- An explanation of the personal data breach, including the form and extent of the respective data concerned, the name and contact details of the site's Data Controller's Data Protection Officer, an estimation of the possible consequences of the personal data breach.

- In addition, a short description of the measures taken by the controller to address the personal data breach, including, where appropriate, to mitigate its possible adverse effects.
- Subjects are to be notified if the personal data breach is likely to result in a high risk to their rights and freedoms, to allow them to take the precautions and enforce legal alterations to protect further damage. Within the scope of this study, no sequencing data or other sensitive high-throughput data is generated. Therefore, the possible effects of a data breach lie within the personal clinical data.
- Specific measures after theft or breaches of personal medical information include the information of the respective authorities, supporting the fast identification of the source of the information breach and support in retrieving the stolen information.

